**2.3 Exploratory objectives:**

Serial peripheral blood and/or tissue specimens will be collected from the enrolled patients who are willing to provide samples for exploratory research. The relationship between biomarkers generated from these serially collected biological samples and treatment efficacy, as well as TRAE, will be extensively investigated.

1. **Subject selection**

**3.1 Inclusion criteria:**

Subjects must meet all of the following inclusion criteria to participate in this study.

1. Age ≥ 18 years old.
2. ECOG performance status 0-1.
3. Histologic or cytologic confirmed NSCLC, stage IV (AJCC 8th).
4. Driver mutations (including EGFR, ALK, and ROS-1) negative.
5. Disease progressed after first-line platinum-based chemotherapy (excluding anti-PD-1/PD-L1 therapy).
6. Subjects with stable or asymptomatic brain metastases can be included, but they must have stable lesions and no neurological symptoms without receiving systemic glucocorticoid therapy.
7. At least 1 lesion with a longest diameter of 1-5cm which was suitable for SBRT at a dose of 24Gy/3Fx, and at least 1 evaluable (RECIST1.1) lesion other than the one to receive SBRT. Lymph nodes can be selected as independent evaluable lesions and SBRT lesions, while brain metastasis cannot be chosen as either SBRT or out-of-field evaluable lesions.
8. Previous radiotherapy is permitted as long as the following conditions were met: 1) SBRT and out-of-field evaluation evaluable lesions must have not received previous radiotherapy; 2) dose received at normal tissue will not be affected by the previous radiotherapy. (Note: If the subject has received previous radiotherapy, detailed radiotherapy-related parameter data should be provided).
9. No palliative radiotherapy was required during study period per investigators’ judgment.
10. Subject who has undergone surgery must fully recover from the toxicity and complications of the surgery before starting treatment.
11. Subjects are encouraged to provide serial blood and tissue samples before and during treatment per protocol requirements.
12. Males/females of child-bearing age should agree to contraception during the trial (surgical ligation or oral contraceptives/intrauterine contraceptives + condoms).
13. Life expectancy ≥ 3 months.
14. Organ function reached the following standards within one week before enrollment:
15. Bone marrow function: hemoglobin ≥ 80 g/L, white blood cell count ≥ 4.0 * 10^9/L or neutrophil count ≥ 1.5 * 10^9/L, platelet count ≥ 100 * 10^9/L;
16. Liver: Serum total bilirubin level ≤ 1.5 times the upper limit of normal (ULN), and aspartate aminotransferase (AST) and alanine aminotransferase (ALT) ≤ 2.5 times ULN. For serum total bilirubin level > 1.5 times ULN, the direct bilirubin level must ≤ ULN;
17. Kidney: serum creatinine level < 1.5 times ULN or creatinine clearance rate ≥ 50 ml/min, urea nitrogen ≤ 200 mg/L, serum albumin ≥ 30 g/L.
18. The subject must have the ability to understand and to voluntarily sign an informed consent form.

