**2.2 Secondary objectives:**

**Treatment-related adverse events (TRAEs):** The proportion of the treatment-related toxic reactions in the total evaluable cases according to the Common Terminology Criteria Adverse Events (CTCAE) 5.0.

**Out-of-field (abscopal) response rate (ASR):** At any time through enrollment to last follow-up, the longest diameter of any un-irradiated target lesions (per RECIST v1.1) reduce ≥30% will be considered as out-of-field (abscopal) response. The ASR is defined as the proportion of patients with an out-of-field response in the total evaluable patients.

**Overall survival (OS):** The time interval from enrollment to death due to any cause. Patients who are still alive at the time of analysis will be censored at the date of last contact.

**Progression free survival (PFS):** The time interval from enrollment to the first documented disease progression or death due to any cause. Patients who are still alive without disease progression at the time of analysis will be censored at the last date of last radiographic follow-up.

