**The principle of lesion selection:**

1. Try to choose lesions with less damage to normal tissues.
2. Try to choose the largest one among all the available lesions, but the size should not exceed 5cm.
3. For bone metastases, if there is no obvious soft tissue mass, they should not be selected for SBRT.
4. Brain metastases should not be selected for SBRT treatment.
5. The lesions that are easier to undergo biopsy should be kept for biopsy, and not be selected for SBRT.

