**6.5.2 Secondary endpoint**

**Treatment-related adverse events (TRAE):** Treatment-related toxic reactions according to the CTCAE 5.0.

**Out-of-field (abscopal) response rate (ASR):** Out-of-field response was defined as reduced by ≥30% of the longest diameter from baseline in any un-irradiated RECIST1.1 evaluable target lesions. ASR was defined as the percentage of patients achieving out-of-field response.

**Overall survival (OS):** The time interval from the first day of enrollment to death from any cause. Patients who are still alive at the time of analysis will be censored by the date of last contact until cut-off date. The Kaplan-Meier method will be used to estimate the survival curves of the two groups, and the median OS (90% two-sided confidence interval) will be calculated.

**Progression free survival (PFS):** The time interval from enrollment to the first documentation of disease progression or death due to any cause. Patients who are still alive without disease progression until data cut-off will be censored by the time of the most recent radiographic follow-up. The Kaplan-Meier method was used to estimate the survival curves of the two groups, and the median PFS (90% two-sided confidence interval) was calculated.

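### Inclusion item 7 asks only for an evaluable un-irradiated lesion, while the abscopal response is scored on un-irradiated target lesions, so a patient who cannot be scored can be admitted

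*Protocol*

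**What the plan says.** Item 7 of section 3.1 sets two lesion requirements. The lesion to be irradiated has a size range: "At least 1 lesion with a longest diameter of 1-5cm which was suitable for SBRT". The second lesion has none; the item asks for "at least 1 evaluable (RECIST1.1) lesion other than the one to receive SBRT". Item 7 adds that "Lymph nodes can be selected as independent evaluable lesions and SBRT lesions", and excludes one type of lesion from both roles: "brain metastasis cannot be chosen as either SBRT or out-of-field evaluable lesions".

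The lesion-selection principles in section 5.1 add a further restriction, but only on the irradiated lesion: "For bone metastases, if there is no obvious soft tissue mass, they should not be selected for SBRT".

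ASR is defined twice. Section 2.2 counts a response when "the longest diameter of any un-irradiated target lesions (per RECIST v1.1) reduce ≥30" per cent, and takes ASR as "the proportion of patients with an out-of-field response in the total evaluable patients". Section 6.5.2 defines the response as "reduced by ≥30% of the longest diameter from baseline in any un-irradiated RECIST1.1 evaluable target lesions", and expresses ASR as a percentage of patients without the word evaluable.

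ORR (sections 2.1 and 6.5.1) is CR or PR by RECIST 1.1. Neither section says that the irradiated lesion is left out of it.

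**The concern.** The second-lesion requirement exists so that every patient has disease outside the field on which an effect of the combination can be seen. To do that, it must select the class of lesion that the endpoint uses. Item 7 says *evaluable*, while the endpoint needs a *target* lesion with a diameter. A multi-center trial screens against the inclusion criteria, so the gap lies in the text that decides who gets in.

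Two things are at stake. ASR is the endpoint closest to the trial's mechanistic hypothesis, and a patient with no un-irradiated target lesion can never count as a responder. For ORR, tumour shrinkage in such a patient could be measured only in the lesion that received 24 Gy, so a response would reflect the direct effect of SBRT.

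**Working it through.** **Step 1. The plan's own figures.** Section 6.1 gives n = 56, success at 17 or more responders, a null ORR of 20%, an alternative of 38%, one-sided alpha 0.0432, power of at least 90%, and 63 enrolled after 10% dropout. By exact binomial:

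- P(X ≥ 17 | 56, 0.20) = 0.0432, as stated.
- P(X ≥ 17 | 56, 0.38) = 0.908, consistent with at least 90%.
- 56 / (1 − 0.10) = 62.2, rounded up to 63, as stated.

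These figures are right and do not depend on the wording of item 7. ASR has no sample size, hypothesis or power of its own in the protocol.

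**Step 2. The texts side by side.**

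- *Size or class of the irradiated lesion:* given (longest diameter 1–5 cm).
- *Size or class of the un-irradiated lesion at entry:* evaluable by RECIST 1.1; no minimum size, no measurable or target requirement.
- *Types barred as the un-irradiated lesion:* brain metastasis only.
- *Bone metastasis without soft-tissue mass:* barred for SBRT; no section bars it as the un-irradiated lesion.
- *Lesion needed to score ASR:* an un-irradiated target lesion with a longest diameter (sections 2.2 and 6.5.2).

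Take a patient with one 3 cm lung lesion chosen for SBRT and, elsewhere, only a bone lesion without a soft-tissue mass. If *evaluable* is read as assessable but not necessarily measurable, item 7 is met. There is then no diameter outside the field on which a 30% reduction can be judged.

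**Step 3. What happens to that patient in ASR.** Section 2.2 divides by total evaluable patients, a term the protocol does not define. Section 6.5.2 divides by patients. The first may drop the patient; the second appears to keep the patient.

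**Step 4. Size if kept.** Let f be the share with no un-irradiated target lesion (assumed, since the protocol gives no figure) and a the rate among patients who can be scored. Reported ASR = a × (1 − f).

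- a = 30% (assumed): f = 5% gives 0.30 × 0.95 = 28.5%; f = 10% gives 0.30 × 0.90 = 27.0%; f = 15% gives 0.30 × 0.85 = 25.5%.
- a = 26.8% (11 of 41 in the radiotherapy plus GM-CSF study described in the protocol's background): 25.5%, 24.1% and 22.8% for the same values of f.

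**Step 5. Size if dropped.** The estimate is then not diluted, but it rests on fewer patients. With a = 26.8% and a starting number of 56, f = 5%, 10% or 20% leaves about 53, 50 or 45 patients. The 95% half-width, 1.96 × √(0.268 × 0.732 / n), goes from 11.6 points at 56 to 11.9, 12.3 and 12.9 points.

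**The case against.** The strongest reply is that the protocol does not use *evaluable* on its own. Item 7 attaches RECIST 1.1 to it, items 7 and 8 use it for the lesion chosen to assess out-of-field response, and section 6.5.2 joins the two words when it speaks of evaluable target lesions. On that reading *evaluable* already means eligible as a target, the RECIST size rule comes with it, and no unscorable patient enters. This reading is open and probably the intended one. It still does not settle the matter, because item 7 does not say it. An SAP cannot repair eligibility after enrolment. Nor does the removal of inappropriately enrolled patients from the efficacy analysis (section 3.3) clearly help, since such a patient meets item 7 as written.

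A second reply is that the denominator in section 2.2 could exclude the patient, and that analysis sets are often defined in the SAP. That is fair as far as it goes: dilution is one reading and not a certainty. But the two ASR definitions in the protocol do not match, and that can be put right in the protocol.

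Three stronger inferences are tempting and are not supported:

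- *That the trial loses power.* This would follow only if the primary endpoint were read on un-irradiated lesions. Sections 2.1, 6.1 and 6.5.1 set no such limit.
- *That admitting lymph nodes makes patients unscorable.* A node has a longest diameter and can be scored under sections 2.2 and 6.5.2. What is open is only whether ASR and ORR measure a node on the same axis. The protocol does not state how nodes are measured for ORR, and any conflict would come from the RECIST standard and not from the protocol's own text.
- *That such patients will certainly be enrolled.* The wording permits it; the document does not show how often it would happen.

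**Conclusion.** The point holds as a mismatch between an eligibility criterion and the endpoint it serves. Read literally, item 7 can admit a patient with no un-irradiated target lesion. Such a patient cannot be scored for ASR and has the irradiated lesion as the only measurable disease for ORR.

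The size is modest and rests on assumptions. If 5 to 15% of patients were affected and kept in the denominator, an assumed 30% ASR would be understated by 1.5 to 4.5 percentage points. If they were dropped, the cost would be some precision. The true share is unknown and may be negligible if sites already read *evaluable* as *target*. ASR is a secondary endpoint. The success rule of 17 of 56, alpha of 0.0432 and power of 0.908 stand. The change is worth making because it is cheap and has to be made in the protocol.

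**What to change.** - **Section 3.1, item 7:** for the lesion other than the SBRT lesion, replace *evaluable* with a requirement for at least one un-irradiated lesion that is measurable per RECIST 1.1 and recorded as a target lesion at baseline.
- **Sections 2.2 and 6.5.2:** use one ASR denominator, worded identically in both places, and define *evaluable patient* if that term is kept.
- **Minor, same sections:** state which axis is used for lymph nodes in ASR, so that it agrees with the measurement used for ORR.

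This is a wording amendment. Sample size, decision rule, alpha and power are unchanged. The downside is that a few patients whose only disease outside the SBRT lesion is non-measurable become ineligible, which may slow recruitment slightly.

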**3.2 Exclusion criteria:**

Subjects who meet any of the following exclusion criteria are not eligible to participate in this study:

1. The subject had received anti-PD-1/PD-L1 inhibitors or other immune checkpoint inhibitors.
2. The subject has severe autoimmune diseases: active inflammatory bowel disease (including Crohn’s disease and ulcerative colitis), rheumatoid arthritis, scleroderma, systemic lupus erythematosus, autoimmune vasculitis (such as Weiger Granuloma), etc..
3. The subject has symptomatic interstitial lung disease or active infectious/non-infectious pneumonia.
4. The subject has any risk factors for intestinal perforation: active diverticulitis, intra-abdominal abscess, gastrointestinal (GI) obstruction, abdominal cancer or other known risk factors for intestinal perforation;
5. The subject has a history of other malignant tumors;
6. The subject has active infection, heart failure, myocardial infarction, unstable angina or unstable arrhythmia within 6 months before enrollment;
7. The subject has physical examination or clinical findings, or other uncontrollable disease, which the investigator believes may interfere with the outcome or increase risk of treatment complications.
8. Palliative radiotherapy is required per investigator’s judgement.
9. The first-line treatment does not include platinum-based chemotherapy.
10. The tumor is mixed with components of small cell lung cancer;
11. Women who are breastfeeding or pregnant.
12. The subject has congenital or acquired immunodeficiency diseases including human immunodeficiency virus (HIV), or a history of organ transplant or allogeneic stem cell transplant.
13. The subject has known hepatitis B virus (HBV), hepatitis C virus (HCV) or active tuberculosis infection.
14. The subject has received oncological vaccines or other vaccines within 4 weeks before the start of treatment.

(Note: Seasonal influenza vaccines for injection are mostly inactivated and therefore are allowed, whereas intranasal vaccines are usually live attenuated vaccines and therefore are not allowed.)

1. The subject uses other immune-agents, chemotherapeutic agents, other drugs in clinical studies, and long-term cortisol during the study period.
2. The subject has mental illness, substance abuse, or social problems that affect compliance are not included after being reviewed by a doctor.
3. The subject is allergic or contraindicated to sintilimab or GM-CSF.

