**3.3 Subject withdrawal/discontinuation criteria:**

1. Inappropriate enrollment. Those who have not received any treatment after enrollment should withdraw immediately, and the subject's information will not be included in the study analysis. If the subject has already received study treatment, the investigator will evaluate the subject and determine the benefit and risk of the subject before deciding whether to withdraw. If the subject needs to be excluded, he/she will be withdrawn from the study after the completion of follow-up after treatment. The subject’s information will not be included in the efficacy analysis of this study, but should be included in the safety analysis.
2. Any of the following situations occur during the pre-treatment evaluation stage: new or deteriorated systemic disease which meet the exclusion criteria, voluntarily withdraw consent or lost to follow-up or death; poor compliance.
3. For those who are considered to be excluded by investigators, the investigator shall report the reasons for the exclusion to the principal investigator. When permitted, patients who have not yet received any study treatment should be withdrawn immediately, and the information of this subject will not be included in the study analysis. If the subject has already received the protocol specified treatment, he/she will be withdrawn from this study after the completion of the follow-up after treatment, and the subject will not be included in the efficacy analysis of this study, but should be included in the safety analysis.
4. Subjects may request withdraw from the clinical trial at any time during the study period if they do not want to continue.
5. If serious adverse events occur, the subject might be withdrawn on the judgment of the investigator.
6. Deterioration during the trial, which may threaten the life of the subject, or other conditions that may affect the observation appear during the trial.
7. The subject lost follow-up or die during the treatment period.
8. The subject received chemotherapy, Chinese medicines, other immunotherapy drugs, radiotherapy sensitizers, or other drugs that affect the efficacy and toxicity evaluation during the trial.
9. Serious deviations which makes it difficult to evaluate the drug effect.
10. Poor compliance.
11. **Study plan and timing of procedures**

[figure not shown]

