**Figure 1. Study flow**

**Table 1. Study schedule**

|  | **Baseline screening** | **SBRT** | **Sintilimab, GM-CSF treatment** | **Sintilimab maintenance** | | **End of treatment**  **Survival follow-up** |
| --- | --- | --- | --- | --- | --- | --- |
| Window (days) | Within 28 days before the start of SBRT | End of SBRT  (or before D1 administration) | C1D1  D5/9/14 (± 2 days) | C2D1  (±3 days) evaluation before each administration | CnD1  (±3 days) | Every 3 months  (±7 days) |
| Frequency |  |  | 3 times in total | Every 3 weeks | Every 9 weeks  (every 3courses of Sintilimab) | Every 3 months |
| **Research procedure** |  | | | | | |
| Informed consent^1^ | X |  |  |  |  |  |
| Inclusion criteria | X |  |  |  |  |  |
| Demography/ Medical history/ Previous treatments^2^ | X |  |  |  |  |  |
| Vital signs ^3^ |  |  |  |  |  |  |
| Weight/Height^4^ | X |  |  | X | X |  |
| Medical history^5^/ Physical examination | X |  | X | X | X | X |
| ECOG PS score | X |  |  | X | X | X |
| Blood routine ^6^ | X |  | X | X | X | X |
| Coagulation function ^7^ | X |  |  | X | X | X |
| Blood Biochemistry ^8^ | X |  | X | X | X | X |
| Thyroid function ^9^ | X |  |  | X | X | X |
| Pregnancy test ^10^ | X |  |  |  |  |  |
| Urinalysis ^11^ | X |  |  | X | X |  |
| Virological antibody testing (HIV, HBV and  HCV) | X |  |  |  |  |  |
| 12-lead ECG | X | when necessary | | | | |
| Lung function | X |  |  |  |  |  |
| Adverse event assessment ^12^ |  | X | X | X | X | X |
| Concomitant medication | X | X | X | X | X | X |
| Subsequent anti-tumor treatment |  |  |  |  |  | X |
| Telephone follow-up (when outpatient follow-up is not possible) |  |  |  |  |  | X |
| **Efficacy evaluation** |  | | | | | |
| Radiographic assessment ^13^ | X |  |  |  | X | X |
| Gene mutation detection ^14^ | X |  |  |  |  |  |
| **Biomarker exploration** |  | | | | | |
| Blood specimens for biomarker studies ^15^ | X | X (end of SBRT) | X | X | X | X |
| Tumor puncture ^16^ | X | X (end of SBRT)  (Recommended, not required) | X (after d14 GM-CSF medication,  Recommended, not required) |  |  |  |

1. The signing of the ICF should be performed before any study procedure.
2. Previous treatments include treatment for the initial diagnosis, including chemotherapy, radiotherapy, and surgical treatment, as well as treatment for previous co-existing diseases within the past 30 days.
3. Vital signs include temperature, pulse, respiratory rate, and blood pressure.

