**Table 3. Suspension and permanent withdrawal of Sintilimab**

a: Resume administration after the symptoms improved to grade 0-1 or baseline level.

b: For hypophysitis, adrenal insufficiency, thyroid insufficiency/hypothyroidism, and type 1 diabetes, Sintilimab can be restarted if they are fully controlled and require only physiological hormone replacement therapy.

c: For abnormal grade 4 laboratory test results, the decision to terminate the medication should be based on the accompanying clinical symptoms/signs and the clinical judgment of the investigator.

The maximum interval allowed for drug suspension is 12 weeks. If it is not possible to return to the state where Sintilimab can be re-used within 12 weeks, the subject will permanently stop Sintilimab and enter the follow-up phase. Except for the following two cases:

1. Due to the application of glucocorticoids in the treatment of irAE, the process of glucocorticoid reduction led to the suspension of Sintilimab for more than 12 weeks. In this case, it is necessary to discuss with the sponsor's medical manager to decide whether to continue Sintilimab treatment. The imaging examination to evaluate the efficacy is carried out as planned, and is not affected by the suspension of medication.

2. Sintilimab was suspended for more than 12 weeks due to treatment related AEs unrelated to Sintilimab. In this case, it is necessary to discuss with the sponsor to decide whether to continue Sintilimab treatment. The imaging examination to evaluate the efficacy is carried out as planned, and is not affected by the suspension of medication.

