**6 Statistical analysis**

**6.1 Calculation of sample size**

This study uses the objective response rate (ORR) as the primary end point. This single-arm study requires 56 eligible patients. Considering a 10% dropout rate, a total of 63 patients will be enrolled.

The research hypothesis is based on Checkmate 017 and Checkmate 057 study, which reported an ORR of 20%. If the ORR of the experimental treatment in this study is 20%, it is not worthy of further study. But if the ORR of the experimental treatment in this study is 38%, the study is considered successful. The purpose of this study is to distinguish ORR between 20% and 38%. The statistical assumptions are: the null hypothesis ORR<=20%, and the opposite hypothesis ORR>=38%. If 17 or more of the 56 eligible patients are CR or PR, this study is deemed successful and is worthy of further study. With a one-sided type one error rate (alpha) equal to 0.0432, this study has at least 90% statistical power to reject the null hypothesis.

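### One exclusion criterion is worded on drug use during an undefined study period, so a treated patient could be ruled ineligible, and leave the 56 that decide success, after response is known

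*Protocol*

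**What the plan says.** Section 3.2 of the protocol opens with "Subjects who meet any of the following exclusion criteria are not eligible to participate in this study". Among the items after the vaccine note it lists "The subject uses other immune-agents, chemotherapeutic agents, other drugs in clinical studies, and long-term cortisol during the study period". The study period is not defined anywhere in the protocol.

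Other parts of the protocol bear on the same events:

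- The text on prohibited concomitant treatment (numbered 5.5.2, within 5.2.7) restricts drugs during the treatment period, a narrower term. It allows corticosteroids for adverse events with an immune cause.
- The notes to Table 3 (section 5.2.2) foresee a case in which "the process of glucocorticoid reduction led to the suspension of Sintilimab for more than 12 weeks", with continuation of sintilimab then open for discussion.
- Table 1 has a row for "Subsequent anti-tumor treatment", marked only in the end-of-treatment and survival follow-up column. Section 6.3 has the last patient followed for 25 months after enrollment.
- Section 3.3, item 1, covers inappropriate enrollment. If a treated patient is to be excluded, that patient's "information will not be included in the efficacy analysis of this study, but should be included in the safety analysis". Item 3 has the same consequence and begins "For those who are considered to be excluded by investigators, the investigator shall report the reasons for the exclusion to the principal investigator". Neither item sets a time limit.
- Section 6.1 sets the success rule: "If 17 or more of the 56 eligible patients are CR or PR, this study is deemed successful".

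**The concern.** An eligibility criterion should be decidable from the patient's state, or from what is planned, at entry. This one refers to what the patient does later. Most other items in section 3.2 that carry a time reference look back from enrollment or from the start of treatment; this one does not.

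Two things follow. First, a patient given steroids for an immune-caused event, as other sections allow, can meet an exclusion criterion after treatment has begun. Second, section 6.1 counts eligible patients without saying when eligibility is settled, and section 3.3 provides a route by which a treated patient leaves the efficacy analysis. In an open-label, single-arm trial with investigator-assessed response, that decision could be taken with the response already known.

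If the patients lost this way are mainly non-responders, the observed ORR rises and the rule of 17 in 56 no longer carries its stated error. The bias could also run the other way: a patient on a long steroid course for an immune event may be a responder. The protocol gives no figure for either group.

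**Working it through.** **Inputs.** All are from section 6.1: null ORR 0.20, alternative 0.38, 56 eligible patients, a bar of 17 responses, one-sided alpha 0.0432, power at least 90%, 10% dropout, 63 enrolled. The number of patients removed later, k, is an assumption.

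**Step 1: reproduce the plan.** With X binomial:

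- P(X ≥ 17 | n = 56, p = 0.20) = 0.0432.
- P(X ≥ 17 | n = 56, p = 0.38) = 0.9076.
- 56 / 0.9 = 62.2, rounded up to 63.

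All the stated figures are correct. The question is only who counts among the 56.

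**Step 2: remove k non-responders.** Suppose 56 + k patients are treated and k non-responders are later ruled ineligible, leaving 56. Taking out non-responders does not change the number of responses, so success occurs exactly when there are 17 or more responses among 56 + k. The true one-sided error is P(X ≥ 17 | n = 56 + k, p = 0.20):

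| k removed | n before removal | one-sided error |
|---|---|---|
| 0 | 56 | 0.0432 |
| 1 | 57 | 0.0505 |
| 2 | 58 | 0.0585 |
| 3 | 59 | 0.0675 |
| 4 | 60 | 0.0772 |
| 5 | 61 | 0.0879 |
| 6 | 62 | 0.0995 |
| 7 | 63 | 0.112 |

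**Step 3: the limit.** The planned margin is 63 − 56 = 7 patients. Ordinary dropout draws on the same margin, so k = 7 is a ceiling and not an expected value.

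**Step 4: the same effect as a share.** If a share f of non-responders is removed and no responders, the apparent ORR under the null is 0.2 / (0.2 + 0.8(1 − f)). The average number removed from 63 is 63 × 0.8 × f.

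- f = 5%: 2.5 removed, apparent ORR 0.2083, error 0.0604.
- f = 10%: 5.0 removed, apparent ORR 0.2174, error 0.0841.

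Both lie within the range of the table.

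**The case against.** The strongest reply is that the protocol treats eligibility as an entry gate. Section 3.2 speaks of eligibility to participate. Table 1 marks the check of inclusion criteria only at baseline screening. Section 3.3, item 2, ties newly meeting the exclusion criteria to the stage before treatment. Section 3.3, item 8, deals separately with chemotherapy during the trial, as a reason for withdrawal, and does not say that such a patient leaves the efficacy analysis. On the steroid conflict, a specific permission would ordinarily qualify a general entry criterion. All this makes planned concurrent use the likely intent. It does not settle the matter, because the text never says so and items 1 and 3 of section 3.3 have no cut-off in time.

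A reader might infer more than the document supports:

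- *That later drug use removes a patient automatically.* It does not. Items 1 and 3 both depend on the investigator's judgement.
- *That every non-responder given chemotherapy after progression becomes ineligible.* This requires the study period to include survival follow-up, which the protocol does not state. It would also sit oddly with Table 1, which plans to record that treatment.
- *That inclusion item 9 has the same fault.* Its words "No palliative radiotherapy was required during study period" are followed by a reference to the investigators' judgement, and an exclusion item mirrors it in the present tense. It is a forecast made at entry.

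The analysis sets may be defined in a statistical analysis plan that is not at hand, so the lack of a definition of eligible or evaluable patients is not the complaint. The wording of an eligibility criterion, and the removal rule in section 3.3, belong to the protocol.

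**Conclusion.** The point holds in a limited form. The exclusion item is worded on events after enrollment, uses an undefined period, and read literally conflicts with the passages on corticosteroids and on the glucocorticoid taper. Nothing in the protocol prevents a treated patient from being ruled ineligible after response is known.

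One non-responder removed takes the one-sided error just past 5%, and the full margin of seven takes it to 0.112. These figures assume that only non-responders are removed, that 56 remain, and that the bar stays at 17. The size of k is assumed, and loss of responders would work in the opposite direction. A reader might extend the share calculation to 15% or 20% of non-responders and obtain a larger error. Those shares mean about 7.6 (63 × 0.8 × 0.15) and 10.1 (63 × 0.8 × 0.20) patients, more than the seven spare, so the planned trial does not support them.

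This is a cheap improvement that protects the stated error rate. It does not show that the error rate has been lost.

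**What to change.** 1. Re-word the exclusion item as a condition known or planned at enrollment, for example that at enrollment the patient is receiving, or is planned to receive, one of the listed drugs.
2. Reconcile that item with the text on prohibited concomitant treatment and with the notes to Table 3, so that use allowed there cannot also count as ineligibility.
3. State in sections 3.3 and 6.1 that eligibility for the primary analysis is judged only on information up to the start of treatment, and that a treated patient is not removed from the ORR denominator because of later drug use or radiotherapy.

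Inclusion item 9 needs no change.

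Since fewer patients would then leave, more than 56 may count, and section 6.1 should say what bar applies in that case. With all 63 counted, 17 responses give a one-sided error of 0.112 and 18 give 0.0657. A bar of 19 gives 0.0362, with power 0.923 at an ORR of 38%.

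The cost is a re-worded criterion and a sentence in each of two sections. The reported ORR may be slightly lower. No extra patients or procedures are needed.
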